The SPADI is a self-report measure of pain and function in patients with shoulder disorders [24]. It is the most commonly used outcome measure in trials of conservative interventions [25]. The SPADI has been validated for use with patients who have shoulder pain. A minimally clinically important change of 10 points has been identified [24, 26]. Additionally, excellent levels of reliability (intraclass correlation coefficient 0.66 to 0.95), high internal consistency (Cronbach’s α typically >0.9) and responsiveness over time have been reported in tandem with no floor and ceiling effects [26]. The SPADI has 13 items divided into two sub-scales: pain (5 items) and disability (8 items). The responses are indicated on a visual analogue scale where 0 = *no pain/no difficulty* and 10 = *worst imaginable pain/so difficult it requires help*. The items are summed and converted to a total score out of 100 where a high score indicates greater pain and disability.

The EQ-5D-5L is a generic measure of health-related quality of life. It provides a single index value for health status that can be used in a clinical or health economic evaluation [27]. The EQ-5D-5L consists of questions relating to five health domains (mobility, self-care, usual activities, pain/discomfort and anxiety/depression) and respondents rate their degree of impairment using five response levels (no problems, slight problems, moderate problems, severe problems and extreme problems) [27]. The EQ-5D-5L is the National Institute for Health and Care Excellence’s preferred measure of health-related quality of life in adults.

A patient-completed personal exercise diary will be returned to the treating physiotherapist at the 4-week follow-up appointment and then returned to Keele CTU. Alternatively, it can be returned to Keele CTU along with the 6-week postal questionnaire, if necessary.

The rate of tendon re-tear or failed healing will be evaluated through a diagnostic USS performed at 12 weeks according to an agreed and standardised protocol for the sonographers. This information will be compared to the pre-operative imaging results and the intra-operative findings. A diagnostic USS is regarded as a relatively cheap but accurate modality for identifying RC tears [28].

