#### Interventions

##### Control group

Reflective of current UK practice [7], after surgery, the patient’s shoulder will be immobilised using a sling for 4 weeks. They will have one session in the hospital with a physiotherapist, after surgery but prior to discharge. This session will include advice to maintain the sling in situ at all times. It should be removed *only* to perform specific daily exercises (table slides, active elbow, wrist and hand exercises and passive shoulder abduction, flexion and lateral rotation movements, within pain limits), or for eating, washing and dressing. The sling should also be worn at night. No further active movement will be encouraged. A post-operative information and exercise booklet with photographs and text detailing the exercise type and number of sets and repetitions will be provided. This initial discussion will be followed up approximately 2 weeks later at an outpatient appointment with the physiotherapist, who will reconfirm this advice.

Adherence to the programme, i.e. time out of the sling, will be measured using a personal exercise diary. This was developed in association with our patient and public involvement and engagement (PPIE) group and will be provided by the physiotherapist. Participants will be asked to record in the diary for how long they were not wearing the sling at regular periods throughout the day, in the same way as the intervention group. Participants will also be asked to record the extent to which they feel they have adhered to the prescribed exercise plan.

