##### Intervention group

The intervention group will undergo early patient-directed rehabilitation. This includes one session in hospital with a physiotherapist, after surgery but prior to discharge. In contrast to the control intervention, this session will include advice to remove the post-operative sling, as pain allows, as soon as possible and gradually to begin actively using the arm within the limits of their pain. This use will increase over time according to agreed goals within the context of the patient’s own pain experience and tolerance. Like the participants in the control group, participants in the intervention group will also receive advice to perform specific daily exercises (table slides, active elbow, wrist and hand exercises, and passive shoulder abduction and flexion movements, all within pain limits). However, given that the intention of the intervention is to encourage early movement after surgery, if participants remove their arm from the sling at times other than to exercise, then they will not need to do the basic table slides and active elbow, wrist and hand exercises. Instead, they will be advised that only shoulder abduction, flexion and lateral rotation movements are required to encourage range of movement. A post-operative information and exercise booklet with photographs and text detailing the exercise type and number of sets and repetitions will be provided.

This initial discussion will be followed up approximately 2 weeks later at an outpatient appointment with a physiotherapist to discuss progress, address barriers to sling removal and active functional shoulder movement, and to facilitate adherence with the early rehabilitation. As with the control group, an assessment of the implementation of and adherence to the intervention will be facilitated by the personal exercise diary, which the participant will use to record the time out of the sling at regular periods throughout the day. Participants will also be asked to record the extent to which they feel they have adhered to the prescribed exercise plan.

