### Statistical analysis plan

As this is a pilot and feasibility RCT, the main analysis will focus on process outcomes and will estimate the number of potentially eligible patients, the number and rate of eligible patients, the consent rate, the overall uptake rate (in relation to the number potentially eligible), the retention rate, follow-up rates for questionnaires and texts, and adherence to the interventions, including time out of sling. We will calculate means and confidence intervals of clinical outcomes (both within- and between-study groups) and determine which outcomes are most sensitive to change. We will evaluate the parameters required to inform the sample size calculation for a future main trial. A detailed statistical analysis plan will be developed by the study statistician and agreed by the trial steering committee.

At the end of the study, we will review the findings and in discussion with the trial steering committee, we will make a recommendation about proceeding to a future main trial. The following success criteria will be used to decide whether to make an application for funding for a main trial:i.)Recruitment rates: Randomisation after consent of 20% or more of eligible patientsii.)Intervention adherence: Difference in time out of sling of 40% or more, i.e. the early rehabilitation (intervention) group will report 40% more time out of the sling than the control group in the first 4 weeks after surgeryiii.)Follow-up rates for the potential main outcome measures >70% for questionnaires at 6 and 12 weeks and weekly for the SMS text messages

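### The self-report diary behind the sling-adherence criterion goes back through the treating physiotherapist by default, which leaves it open to reporting towards each arm's instruction

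*Protocol article*

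**What the plan says.** The measure is the same in both arms. For the control group, "Adherence to the programme, i.e. time out of the sling, will be measured using a personal exercise diary". For the intervention group the source is again the diary, "which the participant will use to record the time out of the sling at regular periods throughout the day". In both arms the diary also asks patients how far they feel they kept to the exercise plan.

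The Data collection section fixes the return route. The diary "will be returned to the treating physiotherapist at the 4-week follow-up appointment and then returned to Keele CTU". The second route is a fallback: "Alternatively, it can be returned to Keele CTU along with the 6-week postal questionnaire, if necessary".

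The advice differs by arm. In the control group, "This session will include advice to maintain the sling in situ at all times", with removal allowed for the listed exercises and for eating, washing and dressing. In the intervention group, "this session will include advice to remove the post-operative sling, as pain allows, as soon as possible". At about 2 weeks an outpatient physiotherapist repeats the control advice, or works on barriers to sling removal in the intervention arm. Under Blinding, no masking is kept once the allocation has been disclosed.

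The diary feeds two decisions. The Sample size calculation is built on a 40% difference in sling use captured by the diaries. In the Statistical analysis plan section, criterion ii is "Difference in time out of sling of 40% or more", and it is explained as what the intervention group will report relative to control over the first 4 weeks.

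**The concern.** The outcome is self-reported, the patient knows the arm, and the expected first recipient is a clinician involved in the patient's rehabilitation. A patient who expects that clinician to look at the diary has a reason to present as compliant. Because the advice runs in opposite directions, compliant-looking reports mean less time out of the sling in one arm and more in the other. The errors add in the difference and do not cancel.

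At stake is a criterion for seeking main-trial funding. The error would favour proceeding. It could not be removed at analysis, because the article names no objective sling-wear measure against which to correct it. The return route is stated in the article, so it is not a detail left to the analysis plan.

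**Working it through.** **1. The plan's own figure.** The article gives 76 randomised, 90% power, one-sided 5%, a 40% difference and 20% missing diary data. It gives no base rates, so 30% v 70% is assumed here.

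- Uncorrected two-proportion formula: n = (1.645·√(2·0.5·0.5) + 1.282·√(0.3·0.7 + 0.7·0.3))² / 0.4² = 24.85 per arm, rounded up to 25.
- With continuity correction: (24.85/4)·(1 + √(1 + 4/(24.85·0.4)))² = 29.6, rounded up to 30 per arm.
- With 20% missing: 30/0.8 = 37.5, rounded up to 38 per arm, or 76 in total.

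The figure reproduces under that assumption. Nothing here disputes 76, and changing who receives the diary does not alter it.

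**2. Direction.** Let each arm's mean report move b towards its advice. Reported difference = (early + b) − (control − b) = true difference + 2b. With opposite advice, the shifts add.

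**3. Size, as illustration only.** The article gives no data on shading, no denominator for the percentage and no SD. Assume 40% means percentage points of the day.

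| Shading per arm | Added to difference | Of 24 h | Of 16 h |
|---|---|---|---|
| 0.5 h/day | 1 h | 1/24 = 4.2 points | 1/16 = 6.3 points |
| 1 h/day | 2 h | 2/24 = 8.3 points | 2/16 = 12.5 points |

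These are totals for shading from any cause, not the share due to the return route.

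**4. Could shifts of this order matter to the criterion?** Assume 30 diaries per arm and a true difference of 30 points. The standard error is SD·√(2/30), and the chance of observing at least 40 points is 1 − Φ((40 − 30 − 2b)/SE).

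| Assumed SD (points) | b = 0 | b = 2.5 | b = 5 |
|---|---|---|---|
| 20 | 0.03 | 0.17 | 0.50 |
| 30 | 0.10 | 0.26 | 0.50 |
| 50 | 0.22 | 0.35 | 0.50 |

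For scale, b = 2.5 points is 0.6 h of a 24-hour day (0.025·24).

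**5. Relative reading.** Criterion ii can also be read as 40% more time than control. The point figures in step 3 do not then apply, but the sensitivity remains. With assumed true means of 25% v 30%, the true excess is 30/25 − 1 = 20%. With b = 2.5 it is reported as 32.5/22.5 − 1 = 44%.

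**The case against.** The strongest reply is that the weakness is unblinded self-report, which exists whoever collects the diary. A sealed envelope leaves patients unblinded and self-reporting, so the illustrated shifts are not what a change of route would recover. This stands. The route is an aggravating factor, and its separate contribution cannot be estimated from the article.

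A reader might infer that the diary goes to the very physiotherapist who prescribed the sling rule. The article does not support that. It says only the treating physiotherapist, and Study training separates ward physiotherapists who first prescribe from outpatient physiotherapists who later assess and treat. They may be different people. What can be said is that the recipient belongs to the team that gave or reinforced the advice.

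The instructions are also less polar than a short summary suggests. Control patients have listed reasons to remove the sling. Intervention patients are guided by pain and agreed goals, with no hourly target to over-report towards. Equal shading in both arms is therefore an assumption.

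Other information on adherence exists: physiotherapist case report forms and interviews at around 4 weeks. Under Feasibility outcomes, however, time out of sling is tied to the diaries, and neither of the other sources is described as an objective wear measure.

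Sealing may be specified in the full protocol or the physiotherapist manual. If so, the sponsor need only confirm it. Finally, criterion ii is one of three, and the recommendation is made in discussion with the steering committee. That limits the consequence but does not remove it.

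**Conclusion.** The point holds as a risk created by a stated design choice. The measure that decides criterion ii and underlies the sample size is an unblinded self-report diary, returned by default through a clinician in the team that advised the patient on sling use. Reporting towards that advice would widen the between-arm difference and favour proceeding.

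It would go too far to say that the route does inflate the difference. The article offers no evidence that such reporting occurs or how large it is. The illustration of 4.2 points (24-hour day) or 6.3 points (16-hour day) per 0.5 h of shading in each arm rests on three assumptions: percentage points, equal shading in the two arms, and the chosen length of day. Only part of it could be due to the route. This calls for a cheap improvement to data handling; the design and the sample size need not change.

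**What to change.** Give each patient a pre-addressed envelope. The patient seals the diary in it and either hands it in at the 4-week visit for forwarding unopened or posts it to Keele CTU. State on the diary that the treating physiotherapist will not read it, and put the same instruction in the physiotherapist manual. Fidelity continues to be recorded on the physiotherapist case report form. When criterion ii is interpreted, acknowledge that self-report bias towards each arm's advice remains possible.

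The cost is envelopes and a few words of text. The downside is that the physiotherapist can no longer check the diary for gaps on the spot at 4 weeks, which matters a little given the 20% allowance for missing diary data. Keeping collection at the visit limits that loss. The article assigns the physiotherapist no use of the returned diary: progression after 4 weeks follows symptom response.

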### The randomisation scheme

Blocked randomisation in a 1:1 ratio will be undertaken remotely using web-based randomisation supported by Keele CTU to ensure allocation concealment. Following confirmation of eligibility, and the receipt of a correctly completed and signed consent form and a completed baseline questionnaire, an authorised research health-care practitioner will access Keele CTU’s secure system to randomise the participant to one of the two treatment arms. The randomisation will be performed using random permuted blocks and will be blocked by recruiting site (block sizes of 2 and 4) to ensure that patients at each centre have an equal chance of receiving either treatment. The allocation will be placed in a sealed opaque gold envelope that is attached to the patient’s medical notes or added as a note to the electronic patient file, according to the local procedure. The envelope or note will be addressed to the physiotherapist who will deliver the treatment.

### Blinding

The participant will be informed of the allocation only by the physiotherapist who will deliver the allocated treatment, and the surgeon will remain unaware of the allocation until after the surgery to minimise the likelihood of withdrawal through knowledge of the allocated intervention. No further measures to blind participants, clinicians, research team or oversight committees will be implemented in this external pilot and feasibility RCT.

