### Data collection

The research health-care practitioner will provide the baseline questionnaire to consenting patients for them to complete themselves. This collects demographic data, general practitioner details, the Oxford Shoulder Score (OSS), the Shoulder Pain and Disability Index (SPADI) and EQ-5D-5L. The patient will be given adequate time and a suitable location to complete the baseline questionnaire. It will be checked for completeness by the research health-care practitioner. The original baseline questionnaire will be sent to Keele CTU and a copy retained in the study site file. Once the baseline questionnaire has been completed and checked, the participant will be randomised to either the intervention or control group.

The size and location of the tear will be recorded, since these may be important determinants of the clinical outcome. This information will be collected by the research health-care practitioner from the pre-operative imaging, ultrasound scan (USS) or MRI, which will typically be available in the medical notes. Due to concerns about the reliability of measurements of the size and location of a tear by imaging alone, the physiotherapist who delivers the allocated treatment will record the intra-operative findings of the size and location of the tear and the completeness of repair as they will typically have access to this information. The completeness of the repair will allow the study team to contextualise the USS 12 weeks post-operatively. Previous studies have been criticised for reporting re-tears only dichotomously, i.e. torn or not, whereas a re-tear identified on an USS might just reflect that the tear was only partially repaired or not repaired at the time of the operation.

The OSS is a 12-item shoulder-specific self-report measure of shoulder pain and function, primarily used to assess the outcome of shoulder surgery in RCTs [21]. The OSS is reliable, valid, responsive and acceptable to patients [21–23]. The items refer to the past 4 weeks. Each has five ordinal response options scored from 0 to 4, with 4 representing the best outcome. When the 12 items are summed, this produces an overall score ranging from 0 to 48, with 48 being the best outcome.

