#### Study training

Research health-care practitioners will be trained in each of the participating centres on the participant eligibility criteria, the approach to recruitment and consent, the requirements for the completion of all study paperwork, good clinical practice as applicable to research and the maintenance of the study site file and study records. Reporting of serious adverse events and adverse events will also be covered.

In addition, the clinical physiotherapists, both those who will initially prescribe the study intervention to patients on a ward in an in-patient setting and those who will subsequently assess and treat patients in an outpatient setting, will be trained prior to the start of recruitment and treatment. Due to the limited number of clinical physiotherapists within the clinical site teams, each clinical physiotherapist will treat patients in both arms. However, given the protocolised nature of the interventions, we do not expect a significant contamination effect and we will include contamination and how to avoid it within the study training.

The focus of this training will be on delivery of the interventions and will be supplemented by a comprehensive manual providing clear treatment protocols and guidance on study paperwork for the clinicians. They will also receive instruction sheets for the exercises, personal exercise diaries for participants and post-operative patient information booklets with information on returning to usual activities, including driving and work. The training will take the form of workshops consisting of information provision, question and answer sessions and role play with regards to supporting the approach to early patient-directed rehabilitation and overcoming any barriers.

The sonographers will undertake the USS of the shoulder at 12-weeks to assess whether the RC has re-torn. The USS will be focused on the RC and details of the RC tear and surgery will be provided, as described above. The sonographers will be provided with information regarding the RaCeR study and will be offered the opportunity to discuss the protocol with the research team. However, because the protocol reflects usual practice in the UK, further formal training will not be routinely offered.

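### The protocol states no measure to keep the 12-week ultrasound reader, or those who classify re-tear, unaware of allocation

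*Protocol article*

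**What the plan says.** All statements below are from the protocol article.

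- **Blinding.** The treating physiotherapist tells the participant the allocation, and the surgeon does not know it until after the operation. The stated purpose is to limit withdrawals. The section then closes the matter: "No further measures to blind participants, clinicians, research team or oversight committees will be implemented".
- **Clinical outcomes.** The 12-week scan is done by a sonographer who is independent of the study. Masking is not mentioned.
- **Study training.** On what the reader receives: "The USS will be focused on the RC and details of the RC tear and surgery will be provided, as described above". On contact with the trial: "The sonographers will be provided with information regarding the RaCeR study and will be offered the opportunity to discuss the protocol with the research team". On preparation: "further formal training will not be routinely offered".
- **Data collection.** The scan is "performed at 12 weeks according to an agreed and standardised protocol for the sonographers" and is compared with the pre-operative imaging and the operative findings. On the latter, "the physiotherapist who delivers the allocated treatment will record the intra-operative findings", including completeness of repair. The study team uses completeness of repair to put the scan in context.
- **The randomisation scheme.** The allocation goes to the physiotherapist in a sealed opaque envelope on the notes or, depending on local procedure, as a note in the electronic patient file.
- **Objectives, Statistical analysis plan, Discussion.** The 12-week rate of re-tear or failed healing is an objective. Event rates are listed among the inputs to the main-trial sample size. Clinical outcomes are to be estimated within and between groups. The Discussion names re-tear as the main worry about early rehabilitation. It is not one of the three success criteria.

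**The concern.** Most of the clinical outcomes are self-reported by participants who know their arm, and little can be done about that. Re-tear on ultrasound is the imaging-based outcome, and it can be read without knowledge of the arm. The protocol provides no means of achieving this.

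Reading the scan also involves judgement. The Data collection section itself points out that a defect on ultrasound may be a repair that was partial or never made, rather than a new tear. Someone must decide which, using the operative findings. A reader or classifier who knows the arm and expects early movement to damage repairs could resolve borderline scans differently in the two arms. One who favours early movement could err the other way. Either would distort the between-arm difference and the event rate carried into main-trial planning. A pilot is also where a masked-reading procedure would be tried out.

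**Working it through.** **1. Who could know the allocation when re-tear is determined**

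| Person | Role | What the protocol says about masking |
|---|---|---|
| Sonographer | Reads the scan | Independent; not said to be masked, not said to be told the arm |
| Participant | Attends the scan | Told the allocation after surgery; not said to be asked to keep it to themselves |
| Study team | Puts the scan in context using completeness of repair | Further blinding expressly ruled out |
| Treating physiotherapist | Records tear size, location and completeness of repair | Knows the arm |
| Surgeon | Generates those findings | Masked until after surgery |

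The reader's masking is therefore left open, with three possible leaks: the participant, the electronic note (no access restriction is described) and discussion with an unmasked team. The classifying team is unmasked by the protocol's own statement. For completeness of repair, a masked source exists but is passed through a recorder who knows the arm.

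**2. Number of scans**

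The protocol gives no number of scans and no expected re-tear rate. Sample size calculation gives 76 randomised and an anticipated follow-up rate of 80%. Its precision statement reproduces: z(0.90) × √(0.8 × 0.2 / 76) = 0.0588, against the stated figure of about 6%. I assume that the same 80% applies to scan attendance: 76 × 0.80 = 60.8, or about 30 per arm at 1:1.

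**3. Effect of reclassifying scans in one arm**

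- One scan: 1/30 = 3.3 percentage points on the between-arm difference, and 1/60 = 1.7 points on the pooled rate.
- Three scans: 3/30 = 10 points on the difference.

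**4. Illustration: no true difference, extra false positives in one arm**

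Let p be the true re-tear rate (assumed 10% to 40%) and f the extra false-positive rate in one arm (assumed 5% or 10%). The observed rate in that arm is p + (1 − p)f, and the apparent difference is (1 − p)f. The 95% half-width is 1.96 × √[p(1 − p)/30 + p′(1 − p′)/30], with p′ the observed rate.

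| p | f | Observed rate | Apparent difference (points) | Odds ratio | 95% half-width (points) |
|---|---|---|---|---|---|
| 10% | 5% | 14.5% | 4.5 | 1.53 | 16.6 |
| 10% | 10% | 19.0% | 9.0 | 2.11 | 17.7 |
| 20% | 5% | 24.0% | 4.0 | 1.26 | 20.9 |
| 20% | 10% | 28.0% | 8.0 | 1.56 | 21.5 |
| 30% | 5% | 33.5% | 3.5 | 1.18 | 23.5 |
| 30% | 10% | 37.0% | 7.0 | 1.37 | 23.8 |
| 40% | 5% | 43.0% | 3.0 | 1.13 | 24.9 |
| 40% | 10% | 46.0% | 6.0 | 1.28 | 25.0 |

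The spurious difference is 3 to 9 points. As an odds ratio it is 1.13 to 2.11, a range that contains the pooled estimate of 1.3 (95% confidence interval 0.72 to 2.2) reported in the Background. In every row the pilot's sampling error is larger. Sampling error shrinks as a trial grows, whereas a reading bias does not, so the bias would matter more if the same procedure went into the main trial.

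**The case against.** A reader might infer that the scan is read by someone who knows the arm. The protocol does not say so. The list of people for whom further blinding is ruled out does not name sonographers, and the article places them outside the study. They are given tear and operative details and study information; allocation is not among the items listed. Details of the operation do not reveal the arm, because the randomised treatment starts afterwards. The envelope or note is addressed to the physiotherapist, and no section says that sonographers consult it. The standardised scanning protocol is a partial safeguard, and that document, which is not shown, may deal with masking. All of this stands, and it limits the point to the absence of a stated measure.

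A reader might also take the physiotherapist's entry for an unmasked assessment of the repair. It is not: the physiotherapist records findings that the surgeon made while masked. What remains is room for selective or interpretive recording, which is a smaller risk.

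Nor is re-tear the only objective outcome. Recruitment, retention and tears not found at surgery are objective too, and process outcomes are the trial's main focus. The open design is a declared choice for a pilot, and no success criterion depends on re-tear.

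The objection does not remove the point. Masking of outcome assessment belongs in a Blinding section. This one has such a section, confines its measures to the period up to surgery, and excludes further measures for the study team that interprets the scan.

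**Conclusion.** The point holds in limited form. The protocol states no measure to keep the ultrasound reader unaware of allocation, and it leaves those who interpret the scan unmasked. The recording of completeness of repair by the treating physiotherapist is a second, weaker route to bias.

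Severity is minor to moderate. Re-tear is a stated objective and a possible input to main-trial planning, but it does not decide whether to proceed. Each reclassified scan moves the between-arm difference by about 3.3 points, and the illustrated bias is 3 to 9 points, against a 95% half-width of about 17 to 25 points. These figures assume about 30 scans per arm, true re-tear rates of 10% to 40%, and 5 or 10 percentage points of extra false positives in one arm. None of these is given in the protocol, and nothing in it shows that any scan would be misread. The figures do not support a claim that the pilot's conclusions would be overturned.

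**What to change.** - **Blinding, Study training and Clinical outcomes:** state that sonographers, and whoever classifies a scan as re-tear, are kept unaware of allocation. The scan request form carries the operative findings only; sonographers have no access to the allocation envelope or note; participants are asked not to disclose their sling or rehabilitation advice; and the sonographer records whether they became aware of the arm.
- **Data collection:** take tear size, location and completeness of repair from the surgeon's operative record, made before the allocation is opened. If the physiotherapist still transcribes them, name that record as the source.

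The cost is a change to the request form and one case report form page. No extra reader, scan or visit is needed, and patient care is unchanged. Masking may be imperfect, since participants can let the arm slip. The recorded unmasking would show how often that happens, which is useful to know before a main trial.
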